# Multicenter randomized controlled trial on the comparison of multi-family therapy (MFT) and systemic single-family therapy (SFT) in young patients with anorexia nervosa: study protocol of the THERAFAMBEST study

**DOI:** 10.1186/s13063-019-3347-y

**Published:** 2019-04-30

**Keywords:** Anorexia nervosa, Adolescents, Systemic family therapy, Multi-family therapy, Randomized controlled trial, Cost-efficiency analysis

## Abstract

**Background:**

Anorexia nervosa (AN) is a serious psychiatric illness that begins most of the time during adolescence. An early and efficacious intervention is crucial to minimize the risk of the illness becoming chronic and to limit the occurrence of comorbidities. There is a global consensus on optimal treatment for adolescents suffering from AN: international guidelines recommend single-family therapy that involves the patient and his/her family. Several family therapy approaches have been developed to date. However, these approaches, which imply a direct questioning of intrafamilial dynamics, are not suitable for all patients and families, and the rates of dropout or poor response to treatment remain quite high. A modality of family therapy has been adapted to AN, known as multi-family therapy (MFT), which consists in bringing together several families whose children suffers from the same illness. Objectives of the present randomized clinical trial are to evaluate whether the implementation of MFT in a multi-disciplinary treatment program for adolescents with AN is at least as efficacious as the use of systemic single-family therapy (SFT), with respect to the evolution of body mass index and other clinical outcomes 12 and 18 months after the start of treatment. A cost-efficiency analysis will also be conducted.

**Methods:**

One hundred fifty patients meeting the inclusion criteria will be randomly assigned to one of the two treatment groups. Patients and their families will receive 10 sessions of therapy spread over 12 months. Body weight, eating disorder and other psychopathology-related symptoms, quality of family relationships, and family satisfaction with treatment will be evaluated during the treatment and at an 18 months follow-up. A cost-efficiency analysis will also be carried out.

**Discussion:**

We hypothesize that MFT is at least as efficacious as SFT, but at a lesser cost. The identification of possible preferential indications for each technique could help the improvement of therapeutic indications for adolescents suffering from AN and contribute to the earliness of intervention, which is associated with a better outcome.

**Trial registration:**

ClinicalTrials.gov, NCT03350594. Registered on 22 November 2017. IDRCB number 2016-A00818-43.

**Electronic supplementary material:**

The online version of this article (10.1186/s13063-019-3347-y) contains supplementary material, which is available to authorized users.

## Background and rationale

Anorexia nervosa (AN) is a psychiatric disorder included among eating disorders with a reported prevalence in women ranging from 0.5 to 2.2% [1]. Pauci-symptomatic forms of AN (i.e., those in which all the diagnostic criteria for AN are not met or only partially met) are 2 to 10 times more frequent than complete forms of AN and account for up to 60% of the patients treated in specialized centers. AN is often associated with psychiatric comorbidities, such as depression and anxiety [2–4], personality disorders [5] and substance abuse [6]. The cost of eating disorders is considerable, as much from individual, familial, and social viewpoints as from an economic viewpoint [7, 8].

According to main international guidelines, involvement of the family in the treatment of adolescents, by means of family therapy, is the recommended therapeutic option [9–11]. Several familial approaches have been developed and implemented over the last decades, among them the Maudsley family-based treatment [12], which is the most commonly implemented form of family treatment to date, and systemic single-family therapy (SFT), which we use in our health care institutions [13]. These modalities have been widely evaluated (see [14] for a review). However, even if studies show better efficacy than other treatments, a significant number of patients do not respond well to this treatment. Across all studies, remission rates are still under 50% 12 to 18 months after the start of treatment. Some families (patients and/or parents) seem reluctant to accept a single-family therapy project, probably because they fear that their family functioning will be challenged or because of an excessive closeness in the therapeutic or family relationships. And even if it is accepted, the single-family therapy approach can fail, particularly as a result of strong resistance to change, substantial family dysfunctions, or serious individual pathologies.

Moreover, economic considerations motivate clinicians and researchers to develop new treatments or improve existing ones to improve efficacy and cost-effectiveness, notably in helping prevent hospitalization, which dramatically increases costs of treatment.

Multi-family therapy (MFT) was thus adapted for adolescents with AN and their families. MFT consists in bringing several families together (generally four to seven) faced with the same pathology (psychiatric or physical) in order to create a therapeutic framework and a social network, or “care community.” This idea came from Laqueur, who believed that the presence of other families could help with the issue of independence, a source of conflict, via an identification process with other families [15, 16]. MFT has been applied to various psychiatric pathologies, such as schizophrenia [17, 18], depression and bipolar disorder [19, 20], and post-traumatic stress disorder [21]. In AN, the first experiences of MFT were published in the late 1980s in Denmark and the USA [22, 23]. The approach was formalized and manualized several years later by the Maudsley team as an intensive outpatient treatment [24–27]. Since that time, several teams have implemented MFT in their clinical settings as an alternative to hospitalization and/or single-family therapy [28–35]. If results from observational studies show that intensive MFT approaches present valuable elements regarding efficacy [27, 28, 33–36] implementation of such a treatment is not always possible in terms of availability and motivation of families or financial and human resources. This is why, in France, other teams have adapted and integrated MFT into their pre-existing standard treatment for children and adolescents suffering from AN [37–40]. There are encouraging results from a first observational study showing good efficacy and high satisfaction with treatment [38]. Implementing MFT could thus increase the therapeutic resources available to the patients and their families.

Even if the international literature upholds MFT as a non-negligible therapeutic tool to prevent relapse and as an alternative to hospitalization, to date and to our knowledge, no study has evaluated MFT in a less intensive format than the Maudsley approach (i.e., outpatient setting) in comparison to another form of family treatment. The THERAFAMBEST study aims to provide new evidence regarding MFT in adolescents with AN and to compare this approach to SFT as it is classically proposed in our care setting, in terms of efficacy, cost, family satisfaction, and clinical outcome.

## Objectives

### Primary objective

The main objective of this trial is to examine whether the implementation of MFT in a multi-disciplinary treatment program for adolescents with AN is at least as efficacious in terms of body mass index (BMI) evolution as the implementation of SFT, 12 months after the start of treatment.

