### Participants

#### Inclusion criteria

All patients treated in outpatient care or hospitalized for AN in one of the three study sites (Pr. [name]’ unit at Institut Mutualiste Montsouris, Paris; Pr. [name]’s unit at the Maison des Adolescents, Cochin Hospital, Paris; Pr. [name]’s unit in Rouen University Hospital) will be offered participation in the study if they (1) have a Diagnostic and Statistical Manual of Mental Disorders fifth edition (DSM-5) diagnosis of AN or a diagnosis of Eating Disorder Not Otherwise Specified (EDNOS), (2) are aged between 13 to 19 years, (3) have been diagnosed with AN or EDNOS before 19 years old, (4) benefit from a social welfare program, (5) live, and their family lives, in Paris and its suburbs or Rouen or in the vicinity of Rouen.

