#### Randomization

All patients who give consent for participation and who fulfill the inclusion criteria will be randomized. Randomization will be centralized and stratified according to the status of treatment at inclusion (outpatient care or hospitalization) and the center. A randomization list will be generated by computer, with blocks of variable sizes, by a statistician independent from the group recruiting or taking care of the patients. The allocation ratio will be 1:1. Results of the randomization will be accessible on the comprehensive software used for the trial (CleanWeb™). Family therapy (MFT or SFT) will start during the month following the randomization.

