#### Statistical methods

Regarding the primary objective, we will compare the evolution of BMI between baseline and after 12 month follow-up in the MFT and SFT groups, using an analysis of covariance (ANCOVA) with BMI at inclusion as a pre-specified co-variable, as well as inpatient status versus outpatient care.

As recommended by the Consolidated Standards of Reporting Trials (CONSORT) guidelines for non-inferiority clinical trials [87], the confidence interval of the intergroup difference of the principal criterion thus obtained will be calculated and represented graphically. The decision to conclude in favor of the non-inferiority of MFT in comparison with SFT will be made only if the upper boundary of the confidence interval is below the chosen non-inferiority threshold of 0.75 kg/m^2^.

It is recommended to carry out a double approach, intention to treat (ITT) and per protocol (PP), for the analysis of the principal criterion in cases of non-inferiority clinical trials [88], as the non-observation of a randomized treatment could reduce differences in efficacy of the two treatments and could therefore bias the trial results. The ITT analysis will include all patients randomized in their randomization group, whatever the treatment they have actually received. The PP analysis will only include patients who have followed at least three sessions without any treatment change or protocol violation. Then, in a sensitivity analysis, we will add age and illness duration to the models as co-variables, as they are important prognostic factors. Finally, if non-inferiority has been demonstrated, the superiority of the MFT treatment over the SFT treatment will be assessed in ITT.

Regarding the secondary outcomes, financial cost and satisfaction will be analyzed for the superiority of the MFT treatment over the SFT treatment. We will compare subject and parent satisfaction with the treatments (as evaluated by the CSQ-8 and ECI) at 12 months using an ANCOVA, with the status of treatment is a co-variable at inclusion (outpatient or inpatient) as a pre-specified co-variable.

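### Non-inferiority is stated for adolescents with AN but tested in AN and EDNOS patients pooled, with no named analysis showing whether it holds in AN

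*Protocol article*

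**What the plan says.** The protocol article names the population in two ways.

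- **Objective.** The primary objective is to show that MFT in a "multi-disciplinary treatment program for adolescents with AN is at least as efficacious in terms of body mass index (BMI) evolution" as SFT at 12 months. The aim at the end of the Background and the description of the MFT groups also speak of patients with AN.
- **Entry.** The Inclusion criteria start from patients under care for AN and then require a "diagnosis of AN or a diagnosis of Eating Disorder Not Otherwise Specified (EDNOS"). They set no weight or BMI condition and no cap on the EDNOS share.
- **Randomization.** Allocation is "stratified according to the status of treatment at inclusion (outpatient care or hospitalization) and the center".
- **Primary model.** Statistical methods specifies an ANCOVA "with BMI at inclusion as a pre-specified co-variable, as well as inpatient status versus outpatient care".
- **Analysis sets.** "The ITT analysis will include all patients randomized in their randomization group". The per-protocol set keeps "patients who have followed at least three sessions without any treatment change or protocol violation".
- **Sensitivity analysis.** Age and illness duration are added.

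Diagnosis appears in none of these elements. Moderator analyses are planned under Secondary objectives and Statistical methods, without naming the moderators.

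**The concern.** The article fixes its strata, covariates, analysis sets and sensitivity covariates explicitly, and the result they produce belongs to AN and EDNOS patients together. The objective would attach that result to AN.

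In a superiority trial, mixing in patients who show less contrast between arms costs power. In a non-inferiority trial it helps the claim, because anything that shrinks the difference makes the margin easier to clear. The plan accepts this reasoning when it justifies running both ITT and per-protocol analyses: departures from the assigned treatment can narrow the difference and bias the result. The per-protocol set does not address the mix of diagnoses, since an eligible EDNOS patient who attends enough sessions remains in it. Adjusting for baseline BMI corrects for prognosis but does not restore a diluted treatment difference.

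What is at stake is the population to which a positive result may be applied. A finding of non-inferiority in AN could rest partly on patients without full AN, and none of the named primary or supporting analyses would reveal it.

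**Working it through.** **Inputs from Sample size:** margin 0.75 kg/m², SD of BMI change 1.45, one-sided 2.5%, power 80%, 60 evaluable per group, dropout 20%, 75 randomized per group.

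**Assumed, because the document does not give them:** the EDNOS share q, taken as equal in both arms, and the treatment difference within EDNOS.

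**1. The plan's own figure.** The normal approximation gives n = 2 × 1.45² × (1.960 + 0.842)² / 0.75² = 58.7, so 59. The exact t calculation gives 60 per group, with power 80.2%. Then 60 / 0.80 = 75. The stated sizes reproduce.

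**2. Effect of pooling.** Write the deficit as SFT minus MFT. Suppose it equals the margin in AN and is zero in EDNOS.

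- Pooled deficit: d = 0.75 × (1 − q)
- SE = 1.45 × √(2/60) = 0.265
- P(declare non-inferiority) = Φ((0.75 − d)/SE − 1.96) = Φ(0.75q/0.265 − 1.96)

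| EDNOS share q | Pooled deficit | P(declare non-inferiority) |
|---|---|---|
| 0% | 0.750 | 2.5% |
| 10% | 0.675 | 4.7% |
| 20% | 0.600 | 8.2% |
| 30% | 0.525 | 13.3% |
| 40% | 0.450 | 20.4% |
| 60% | 0.300 | 39.7% |

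Under the same assumption, a pooled deficit at the margin corresponds to an AN deficit of 0.75/(1 − q): 0.94, 1.25 and 1.88 kg/m² at 20%, 40% and 60%.

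**3. Sensitivity.** If the AN deficit is 1.0 kg/m² instead, the probabilities at 20%, 40% and 60% are 1.6%, 8.2% and 26.2%. A mixture was also simulated with 60 per arm, assumed AN gains of 2.0 (SFT) and 1.25 (MFT), and an assumed gain of 0.5 in both EDNOS arms. It gave 7.7–8.0%, 18.1–21.8% and 35.0–45.4% at the same shares, for an EDNOS SD between 1.45 and 1.0.

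**4. When nothing is masked.** If the MFT deficit in EDNOS is as large as in AN, or larger, d is at least 0.75 and the probability does not exceed 2.5%. A small BMI gain in EDNOS does no harm by itself. Only a smaller difference between arms does.

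**5. Precision of a full-AN estimate.** With 60 evaluable per arm, 60 × (1 − q) have full AN. At q = 60% that is 24 per arm: SE = 1.45 × √(2/24) = 0.419 and the 95% half-width is about 0.84 kg/m², wider than the margin. If the therapies are truly equal, the chance that the full-AN interval excludes 0.75 is 70.8% at q = 20%, 58.1% at 40% and 41.9% at 60%.

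**The case against.** Much of the opposing case stands.

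- **Entry is not open to any EDNOS patient.** The Inclusion criteria begin from patients under care for AN, so many EDNOS entrants may have incomplete AN and respond much as full AN does. The description of the EDI-2 lists EDNOS beside bulimia nervosa and binge eating disorder, but it describes what a questionnaire covers and does not define the trial population.
- **The 60% is not a forecast.** The Background says incomplete forms of AN "account for up to 60% of the patients treated in specialized centers". That is a general ceiling. It also concerns forms of AN, and nothing in the document says that these patients lack room to gain BMI. A reader might infer that most of the sample could be patients in whom BMI cannot separate the therapies; the text does not support that.
- **The breadth is deliberate.** The Discussion says so, and for the population actually enrolled the test keeps its 2.5% level. A reader might infer that the primary test is invalid or that an inferior MFT is likely to pass. Neither follows.
- **Moderator analyses are planned.** Diagnosis could be among the moderators, and a condensed article may leave the list to the analysis plan. It would be wrong to say that diagnosis cannot be examined.

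The mismatch itself is left unanswered. EDNOS is still listed as an alternative to AN, the objective still says AN, and an unspecified moderator analysis does not limit the primary conclusion.

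**Conclusion.** The point holds as a mismatch between claim and test population. As written, the plan would support a non-inferiority statement about AN from a pooled AN and EDNOS sample, and any dilution would favour that statement.

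The size is conditional. The chance of a wrong claim for AN runs from about 5% at a 10% EDNOS share to about 40% at 60%, but only with an AN deficit equal to the margin and no difference between arms in EDNOS. If EDNOS patients behave like AN patients, there is little or no inflation. The figures show how far the wording could mislead; they do not predict this trial's error rate. The matter deserves correction because the remedy is cheap and settles what the trial may conclude.

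**What to change.** Keep the broad entry criteria and change the wording and analysis as follows.

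1. State the population as AN or EDNOS in the primary objective and in the non-inferiority conclusion.
2. Add baseline diagnosis to the primary or the sensitivity model as a prognostic covariate. It is already recorded, through the entry criteria and the baseline Short-CIDI. State that this adjustment does not remove dilution.
3. Pre-specify, as a supporting analysis, the MFT-SFT difference with 95% CI in full AN, together with the treatment-by-diagnosis interaction.
4. Fix the rule in advance: after a positive pooled result, claim non-inferiority for full AN specifically only if the full-AN interval also excludes the 0.75 kg/m² margin. Otherwise restrict the claim to the mixed population.

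This needs no new patients, data or change to randomization. The cost is precision: if the EDNOS share is high, the full-AN interval is wide (half-width about 0.84 kg/m² at 60%), and a true claim for AN would often go unsupported. The conclusion would then have to stay with the mixed population.

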### Secondary objectives

Secondary objectives are as follows:To examine whether adding an MFT to a multi-disciplinary treatment program for adolescents with AN is at least as efficacious as SFT, 12 months after the start of treatment, in terms of clinical evolution, evaluated by other clinical outcomes (global clinical state, weight status, menstruation, eating disorder symptoms, anxiety, depressive and obsessive symptoms, social adaptation, family relationships, number and duration of hospitalizations after inclusion, subject and parents’ satisfaction, and parental relief)To study the cost of implementation of each technique in a multi-disciplinary treatment program for adolescent AN, through a cost-efficiency analysisTo identify possible preferential indications for each technique with the help of moderating and prognostic factors for the evolution of AN in psychiatric, physical, and social termsIn case of the non-inferiority of MFT, to test its superiority in comparison with SFTTo carry out a follow-up 6 months after the end of treatment on the same evaluation criteria.

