## Hypotheses

We hypothesize that MFT is at least as efficacious as SFT in terms of weight and clinical evolution, and will be better accepted and not as costly in our treatment program.

We also hypothesize that some patient profiles will have better indications for one or another form of therapy.

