### Statistics

#### Sample size

One hundred and fifty patients and their parents will be recruited.

Power calculation for the primary endpoint of this study is based on the assumption that MFT is not less effective than SFT if a minimal clinical difference of 0.75 kg/m^2^ in mean change of BMI between baseline and 12 months follow-up cannot be shown between groups. The principal judgement criterion*,*
*i.e*., the variation of BMI 12 months after the beginning of treatment, was established after having reviewed family therapy trials and recent trials on AN, whether in the field of family therapy or in other therapeutic trials ([85]). The non-inferiority margin of 0.75 kg/m^2^ is based on clinical experience and is consistent with the scientific literature. The standard deviation of the BMI variation is estimated at 1.45 [85, 86].

Consequently, we determined the size of the sample for a unilateral Student’s *t* test with a significance of 2.5% and a power of 80% with the non-inferiority margin clinically determined for a minimum BMI difference of 0.75 kg/m^2^, assuming the standard deviation to be 1.45.

This procedure led to a required sample size of 60 patients per group. Assuming that the dropout rate is 20% [86], we calculated a sample size of 75 patients per treatment group.

With a total active file of more than 500 patients in the three study sites, we expect to complete the recruitment of 150 eligible patients in 2 years.

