In order to compare financial costs between SFT and MFT, we will make an inventory of the treatments, and we will use the average cost for each ambulatory appointment (psychiatrist, psychologist, etc.) and the average treatment cost for hospitalization if necessary during follow-up; the sum will determine the total cost of treatment for each patient. Transport costs and other associated costs will not be estimated, as most patients live near the hospital. Costs for the two treatment groups will be compared using Fisher-Pitman’s test.

An analysis of quantitative variables (assessment scores) will be performed in the same way as for the principal criterion using an ANCOVA, with the value of each respective variable at admission, and for the status of treatment at inclusion (ambulatory care or hospitalization), as co-variables. Morgan- Russell GOAS scores (with the three following outcomes: good, intermediate, and poor) will be compared between SFT and MFT, using Cochran-Armitage’s tendency test. A measure of ordinal association (Somers’ *D*) will be calculated with a confidence interval of 95%. Amenorrhea and other qualitative variables will be compared using Fisher’s exact test. Additionally, for the clinical variables assessing outcome, analyses looking for moderators and treatment effect mediators will be carried out.

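### The secondary objective asks a non-inferiority question of the other clinical outcomes, but no margin is given for them and the tests fixed for the categorical ones only look for a difference

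*Protocol article*

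**What the plan says.** The protocol article describes a non-inferiority trial. Its Secondary objectives section carries the non-inferiority wording beyond BMI: it asks whether MFT "is at least as efficacious as SFT, 12 months after the start of treatment, in terms of clinical evolution, evaluated by other clinical outcomes". The list that follows includes global clinical state, weight status, menstruation, symptom scales, family relationships, hospitalizations and satisfaction. The Hypotheses section repeats the idea: "We hypothesize that MFT is at least as efficacious as SFT in terms of weight and clinical evolution".

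The tools for a non-inferiority conclusion appear once, for BMI change. Under Sample size, the margin of 0.75 kg/m² "is based on clinical experience and is consistent with the scientific literature". Under Statistical methods, non-inferiority is concluded "only if the upper boundary of the confidence interval is below the chosen non-inferiority threshold".

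For the secondary outcomes, Statistical methods fixes the following:

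- **GOAS category:** scores "with the three following outcomes: good, intermediate, and poor) will be compared between SFT and MFT" by the Cochran-Armitage test, with Somers' D and its 95% confidence interval.
- **Binary outcomes:** "Amenorrhea and other qualitative variables will be compared using" Fisher's exact test.
- **Quantitative scores:** ANCOVA adjusted for baseline value and treatment status, handled as the primary outcome is.
- **Cost and satisfaction:** "financial cost and satisfaction will be analyzed for the superiority of the MFT treatment over the SFT treatment".

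**The concern.** A test of difference has equality as its null hypothesis. Failing to reject equality does not show that MFT is no worse, because the data may simply be too few. To show that MFT is no worse within a stated tolerance, one needs that tolerance and an interval to set against it. For menstruation, weight status and the other qualitative outcomes, the article states a non-inferiority question and fixes a test that cannot answer it.

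What is at stake is the reporting. If these comparisons come out non-significant, the stated objective invites the conclusion that MFT is no worse on menstruation or global outcome, when the trial may not have excluded a deficit that clinicians would care about. One sentence under Sample size reasons this way for BMI: it treats MFT as not less effective if the 0.75 kg/m² difference cannot be shown. For BMI, the interval rule under Statistical methods replaces that reasoning. For the secondary outcomes nothing does.

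**Working it through.** **1. The plan's own figure.** Inputs from Sample size: margin 0.75 kg/m², one-sided 2.5%, power 80%, and "The standard deviation of the BMI variation is estimated at 1.45". With no true difference, the normal approximation gives

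n per arm = 2 × (1.96 + 0.8416)² × 1.45² / 0.75² = 2 × 7.849 × 2.1025 / 0.5625 = 58.7, so 59.

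The exact noncentral t calculation gives 60 (power 80.2%; 59 gives 79.6%). With 20% dropout, 60 / 0.80 = 75. The stated 60 and 75 per group reproduce, so the primary sample size is not in question.

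**2. Objective against method, outcome by outcome.**

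| Outcome | Question in Secondary objectives | Method fixed | Margin in the article | Can the method answer the question? |
|---|---|---|---|---|
| Menstruation and other qualitative variables | MFT no worse | Fisher's exact test | None | No |
| GOAS category | MFT no worse | Cochran-Armitage, plus Somers' D with 95% CI | None | The test cannot; the interval has no threshold |
| Quantitative scores | MFT no worse | ANCOVA, as for the primary | None | Gives an interval, but no verdict |
| Satisfaction | MFT no worse | ANCOVA, for superiority | None | Different question |

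**3. How often a real deficit would be non-significant.** The article gives no event rates or standard deviations for secondary outcomes. The Background says only that remission rates in past studies are below 50%. The 50% rate under SFT and the deficits below are therefore assumptions. The analysed number is taken as 60 per arm (after the planned dropout) or 75 (all randomized). All tests are two-sided at 5%.

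Binary outcome, Fisher's exact test, by exact enumeration of two binomials:

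| True MFT deficit from 50% | Non-significant, 60 per arm | Non-significant, 75 per arm |
|---|---|---|
| 10 points | 84% | 79% |
| 15 points | 68% | 58% |
| 20 points | 46% | 33% |

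Continuous score, unadjusted t test, by the noncentral t distribution:

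| True MFT deficit | Non-significant, 60 per arm | Non-significant, 75 per arm |
|---|---|---|
| 0.2 SD | 81% | 77% |
| 0.3 SD | 63% | 55% |
| 0.4 SD | 42% | 32% |
| 0.5 SD | 23% | 14% |

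**4. What an interval would show.** For a 50% rate, the 95% half-width is 1.96 × √(2 × 0.25 / 60) = 0.179 with 60 per arm and 1.96 × √(2 × 0.25 / 75) = 0.160 with 75. Even with identical observed rates, deficits of up to about 16 to 18 points would not be excluded. For an unadjusted score the half-width is 0.36 SD with 60 per arm and 0.32 SD with 75.

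**5. Margins the trial could support.** With no true difference and 80% power, the smallest margin for a score is √(2 × 7.849 / n) in SD units: 0.51 SD for n = 60 and 0.46 SD for n = 75. For a 50% rate, multiply by 0.5: about 26 points and 23 points. A 15-point margin would need 2 × 0.25 × 7.849 / 0.15² = 174.4, so 175 per arm.

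**The case against.** A reader might infer that the plan intends to call a non-significant secondary result non-inferior. The document does not support this. It sets no such rule for secondary outcomes, and its only operative decision rule, for BMI, is the correct one. The objective is phrased as something to examine, and the Discussion restates the secondary aims neutrally, as new comparative evidence.

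It would also be wrong to say that every secondary outcome gets only a difference test. Handling the scores as the primary is handled can be read as including the confidence interval, and GOAS has Somers' D with a 95% interval. Baseline adjustment would usually make the score comparisons more precise than the unadjusted figures above. The Fisher figures apply to binary outcomes such as menstruation, not to the three-level GOAS category. Finally, this is a condensed article, and margins may stand in a full protocol or analysis plan that is not shown.

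All of that stands and limits the point. It does not remove it. A margin held elsewhere would not turn Fisher's test or Cochran-Armitage into a non-inferiority analysis, and the article fixes those tests itself. An interval without a threshold estimates the difference but gives no non-inferiority verdict. The conflict over satisfaction also lies within the article: superiority fits the Hypotheses section, which expects MFT to be better accepted, but not the list under Secondary objectives.

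**Conclusion.** The concern holds as a mismatch between a stated objective and the methods fixed for it. It is clearest for menstruation and the other qualitative variables, where only Fisher's test is named. It is milder for GOAS category and for the scores, where an interval is planned or can be obtained but has no threshold. Satisfaction is placed under two different questions.

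The risk is an unsupported reading that the article leaves open, not one that it prescribes. Under an assumed 50% SFT rate and 60 to 75 analysed per arm, a true 15-point deficit would be non-significant 58% to 68% of the time and a 20-point deficit 33% to 46%. Other rates would change these figures. The primary conclusion and the sample size are unaffected.

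**What to change.** - Reword the secondary objective, and the matching hypothesis, as estimating the difference between MFT and SFT on the other clinical outcomes.
- Add a risk difference or odds ratio with its 95% confidence interval to each Fisher comparison. Report the adjusted difference with its 95% interval for the scores, and keep Somers' D with its interval for GOAS category.
- State that a non-significant test will not be described as showing that MFT is non-inferior, equivalent or no less effective.
- If the sponsor wants such a claim for one or two key outcomes, fix and justify a margin for each before unblinding and judge by the interval. At this sample size, 80% power is available only for margins near 0.5 SD, or about 25 points on a 50% rate.
- Reconcile satisfaction: either remove it from the non-inferiority list under Secondary objectives or change the superiority statement under Statistical methods.

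The cost is wording and a few added intervals, with no new data or patients. The downside is a more modest claim on the secondary outcomes.
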